### Statistical analysis

2.3

The analysis of all data are carried out with the IBM SPSS Statistical software Windows version 20 (IBM Corp., Armonk, NY). Afterwards, all the data are described with appropriate characteristics such as mean, median, standard deviation as well as percentage. Continuous and categorical variables are analyzed using the independent *t*-tests and *χ*2-tests. For the significance level, the value of *P* needed to be less than .05.

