## Materials and methods

2

The experiment is a randomized clinical research which will be implemented from May 2021 to October 2021 at the First Affiliated Hospital of Soochow University, in accordance with the purposes of the Declaration of Helsinki. The experiment was granted through the Research Ethics Committee of the First Affiliated Hospital of Soochow University (No.100238765) and recorded in research registry (researchregistry 6143). The recruited patients are given the written informed consent before registration. Fifty neurogenic bowel dysfunction patients after SCI confirmed via the imaging are included in this study. The patients with the history of bowel diseases or patients who are unwilling to cooperate with the evaluation will be excluded. Via utilizing the number table, all the patients involved in the experiment are assigned a random number in a random envelope, and the allocation results are hidden from them. The patients are randomly divided into control group (25 cases) and study group (25 cases).

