### Nursing in both groups

2.1

In control group, the patients are given the routine nursing, containing psychological nursing and the education of disease health. The patients are guided to eat more foods with high dietary fiber, fresh fruits and vegetables, drink more water, facilitate intestinal patency, and eat less candies and milk that are prone to gas production, so as to decrease abdominal distension.

Nursing in study group involves:

(1)Quantitative evaluation: on the basis of the imaging examination results and clinical symptoms, the patients are scored in severe, moderate and mild.(2)Individualized nursing intervention:a.Reduce the intake of high-protein and high-fat food. If conditions permit, the daily intake of liquid should be at least 2000 ml.b.Implement an abdominal massage to speed up defecation. While massaging, patients are in the supine position. Centering on the navel, the nurse utilizes one or both hands’ fingers to circle the anatomical position of the colon from right to left, lasting for twenty minutes.c.Exercise muscles involved in the defecation: guide the patients to exercise their abdominal muscles. The patient is in the bed slope position or sitting on the toilet. Abdominal muscles are trained via abdominal breathing, deep breathing as well as defecation. Instruct the patient to perform the anal contraction exercises correctly. The patients’ knees slightly flexed apart with legs together and is in a supine position. Subsequently, patients raise buttocks and then contracts anus as instructed. In the process of anus contraction, the thigh muscle and perineal muscle contract for 6 seconds and relax for 4 seconds.d.Stimulate anus, facilitate colorectal reflection: the action of anal can stimulate intestinal peristalsis. The nurse put on gloves, lubricate middle finger and index finger with the liquid paraffin, inserts into anus slowly and then rotates in rectum. Anal action is implemented daily for 2 minutes.

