### Outcome

2.2

The primary outcomes are bowel function recovery and satisfaction of the patients. The secondary outcomes are quality of life evaluated by SF-36 questionnaire.^[12]^ The questionnaire involves physical pain, role physiology, physiological functions, social functions, vitality, general health, mental health, and role-motional.

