## Result

3

Comparison of clinical parameters between the 2 groups will be shown in Table 1.

**Table 1 T1:** Comparison of clinical parameters between the 2 groups.

Study group (n = 25)	Control group (n = 25)	*P* value
Bowel function		
Abdominal distension		
Constipation		
Defecation time		
Fecal incontinence		
Quality of life		
Physical functioning		
Role-physical		
Bodily pain		
General health		
Vitality		
Social functioning		
Role-motional		
Mental health		

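### One fixed test per variable class leaves no place for ordered or skewed outcomes; at 25 per arm this costs 0 to about 25 points of power, depending on scales the article does not state

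*Protocol article*

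**What the plan says.** Section 2.3 (Statistical analysis) has two relevant sentences. The first concerns description only: "all the data are described with appropriate characteristics such as mean, median, standard deviation as well as percentage". The second sets the tests: "Continuous and categorical variables are analyzed using the independent" t-test and the chi-square test, one for each class of variable. For significance, P "needed to be less than .05"; whether the tests are one- or two-sided is not stated. No trend, rank, ordinal or transformed analysis is mentioned.

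The outcomes that these tests serve are only named. Section 2.2 (Outcome) states: "The primary outcomes are bowel function recovery and satisfaction of the patients", without a scale for either. Table 1, titled "Comparison of clinical parameters between the 2 groups", breaks bowel function down into distension, constipation, "Defecation time" and incontinence, with no levels, units or expected distribution. Satisfaction has no row.

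The only grading in the article is in section 2.1: "the patients are scored in severe, moderate and mild". It is the first step of the study-group nursing and is not described as an outcome. Section 2 fixes 25 patients in each arm.

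**The concern.** The rule in section 2.3 depends only on whether a variable is continuous or categorical. Two common kinds of outcome fit it badly.

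- **Ordered grades.** A Pearson chi-square test on K grades spreads its sensitivity over K − 1 degrees of freedom and gives the same answer if the grades are shuffled. A treatment that moves patients steadily towards better grades is detected more readily by a test that uses the order.
- **Right-skewed times.** A time cannot be negative and may have a long upper tail. A few long values then inflate the standard deviation in a raw-scale t-test.

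Satisfaction, the bowel symptoms and defecation time could each be of one of these kinds. With 25 per arm there is little power to spare, and the Discussion itself names the small sample as a limitation. At stake is the chance of detecting a real effect, not the false-positive rate.

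**Working it through.** **Inputs from the article:** n = 25 per arm (section 2); level 0.05, t-test and chi-square test (section 2.3). **Assumed:** two-sided tests and all outcome distributions and effects below. The article states no power, effect size, SD or event rate, so it has no figure of its own to reproduce.

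**1. How much power there is.** Normal approximation for two means: power = Φ(d√(n/2) − 1.96).
- d = 0.8: 0.8 × √12.5 = 2.828; Φ(0.868) = 80.7%.
- d = 0.5: 0.5 × √12.5 = 1.768; Φ(−0.192) = 42.4%.

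For 60% v 30%, with a pooled null variance: (0.30 − 1.96 × √(2 × 0.45 × 0.55/25)) / √((0.24 + 0.21)/25) = (0.300 − 0.276)/0.134 = 0.18; Φ(0.18) = 57.2%.

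**2. Ordered grades.** Model: the cumulative odds in the study arm equal the control odds times OR. Example, four grades 15/30/35/20% with OR 3: control cumulative odds 0.176, 0.818 and 4 become 0.529, 2.455 and 12, which gives 35/36/21/8% in the study arm. Pearson chi-square (K − 1 df) was compared with Wilcoxon rank-sum (midranks), 20,000 simulated trials per setting. Entries are chi-square v Wilcoxon power, in %.

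| Control grades (%) | OR 2 | OR 4 | OR 8 | Gain over all settings run (points) |
|---|---|---|---|---|
| 3: 20/40/40 | 19.3 v 25.3 | 61.9 v 73.0 | 93.0 v 96.5 | 3.0 to 11.1 |
| 4: 15/30/35/20 | 16.4 v 26.5 | 56.8 v 75.2 | 91.1 v 97.2 | 6.1 to 18.4 |
| 5: 10/20/30/25/15 | 14.8 v 27.2 | 51.4 v 76.2 | 88.5 v 97.6 | 9.1 to 24.8 |

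The last column covers OR 2 to 8 and other control distributions with the same number of grades. In the four-grade example at OR 3, power is 38.0% v 55.7%.

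**3. Binary items.** There is no order to ignore. The squared tie-corrected Wilcoxon statistic equals (N − 1)/N = 49/50 of the uncorrected chi-square, so the two are practically the same test and the loss is 0.

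**4. Skewed time.** Lognormal data, shift of 0.5 to 1.0 SD on the log scale, 20,000 trials per setting.

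| Log-SD (skewness) | Raw t, 0.8 SD | Log t, 0.8 SD | Rank, 0.8 SD | Log minus raw, all shifts | Rank minus raw, all shifts |
|---|---|---|---|---|---|
| 0.3 (0.95) | 76.9% | 78.7% | 76.2% | 1.1 to 1.8 | −1.4 to −0.5 |
| 0.5 (1.75) | 75.0% | 79.9% | 77.3% | 3.0 to 5.0 | 0.9 to 2.3 |
| 0.7 (2.89) | 70.2% | 79.4% | 76.5% | 6.6 to 9.2 | 4.4 to 6.3 |
| 1.0 (6.18) | 60.1% | 79.0% | 76.3% | 13.1 to 18.9 | 10.6 to 16.2 |

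**5. Cost of a rank test if the data are normal.** d = 0.5: 40.9% (t) v 38.6% (rank); d = 0.8: 79.2% v 76.7%. The loss is 2 to 3 points.

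**6. Type I error of the planned tests.** With no effect, chi-square rejected in 4.2 to 5.1% of trials and the raw t-test in 3.9 to 5.0%.

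**The case against.** The strongest reply is that the premises are not in the article. It does not say that symptoms or satisfaction are graded, or that defecation time is skewed. If symptoms are yes/no, chi-square is suitable. If satisfaction is a total score, it goes to the t-test and the argument about order falls away. This stands in full, and it is why the loss can only be given as conditional.

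Three stronger readings fail for the same reason.
- A reader might infer that this trial will lose a definite amount, say 5 to 20 points. The article supports no single figure.
- A reader might take the mention of medians as a sign that the sponsor expects non-normal data. It is one item in a generic list of summaries and chooses no test.
- A reader might treat the mild-to-severe score as the outcome scale. It belongs to the intervention.

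It can also be said that the plain tests are valid and that a log-scale analysis answers a different question. Both are true. A raw t-test properly targets the difference in mean time, whereas the log scale gives a ratio of geometric means. That makes the change for defecation time a choice and not a correction.

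Finally, the treatment of ordinal or skewed data may be left to a full protocol or SAP that is not shown. This carries weight against a complaint of missing detail. But section 2.3 is not silent: it states one test per variable class, and that rule can be judged as it stands.

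**Conclusion.** The point holds in conditional form. Section 2.3 assigns every categorical outcome to chi-square and every continuous one to a t-test, whatever the outcome's scale or shape. At 25 per arm and two-sided 5%:

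- three to five ordered grades: about 3 to 25 points of power lost against a rank test;
- yes/no items: no loss;
- lognormal defecation time: about 1 to 5 points lost against a log-scale t-test at log-SD 0.3 to 0.5, 7 to 9 at 0.7, and 13 to 19 at 1.0.

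The ordinal figures assume proportional odds, a shift in one direction that suits a rank test; an effect that does not follow the order would change them. Because the planned tests keep their type I error near 5%, a reader should not conclude that they are invalid. This is a minor, inexpensive improvement in efficiency.

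**What to change.** In section 2.3, before any data are seen, state that every outcome recorded in ordered grades is analysed by Wilcoxon rank-sum (or proportional-odds regression) and that chi-square is kept for binary or unordered items. Worded this way, the rule can be adopted now, although the scale of each outcome must be stated before one can tell which items it covers.

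Optionally, add that defecation time is analysed on the log scale, reported as a ratio of geometric means with a 95% confidence interval, or by Wilcoxon.

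The cost is one or two sentences, with no extra patients or data and with methods available in the software already named. The downsides belong to the optional part: a log-scale result is a ratio rather than a difference in mean time, and a rank test gives up about 2 to 3 points of power if the times turn out to be normal.

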## Discussion

4

The bowel dysfunction is one of the most familiar problems in the patients with SCI.^[13,14]^ In the early injury stage, the anal sphincter and rectum internal layer are in the stage of total incontinence. After the acute phase, the voiding reflex recovers with the recovery of the lumbosacral central spinal cord.^[15]^ The right side of colon and the bowel are peristalsis supplied by the vagal innervation, so that the feces can be transported to large intestine. After the SCI, patients may have several problems, for instance, reduced sensation and muscle strength, and impaired respiratory as well as other functions.^[16]^ Specifically, SCI can lead to the high spasticity and paralysis of anal sphincter, or lead to the voiding dysfunction. The participation of pelvic and abdominal muscles and effective movement of bowel are essential for the normal defecation. According to the severity of intestinal dysfunction and SCI, we develop a set of nursing intervention based on the quantitative evaluation for the intestinal dysfunction patients after SCI, so as to make nursing more efficient and targeted. Nevertheless, insufficient research design and small size of sample are the limitations of this experiment. The effectiveness of nursing intervention based on quantitative evaluation needs further study.

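### The only test named for continuous outcomes is an unadjusted t-test; adjusting for a starting value would be a cheap gain in a 50-patient trial about recovery

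*Protocol article*

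**What the plan says.** All references are to the protocol article.

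- **Statistical analysis (2.3):** "Continuous and categorical variables are analyzed using the independent" t-test and the chi-square test. The P value "needed to be less than .05". No covariate, change score or adjusted estimate is named.
- **Outcome (2.2):** the primary outcomes are "bowel function recovery and satisfaction of the patients". On the secondary side, "The secondary outcomes are quality of life evaluated by SF-36 questionnaire", which has eight domains.
- **Result (3):** "Comparison of clinical parameters between the 2 groups will be shown in Table 1". That table has one column per group and a P value. It has no baseline, change or adjusted-difference column. Its bowel function rows are abdominal distension, constipation, defecation time and fecal incontinence, with no scale given for any of them.
- **Materials and methods (2):** 50 patients, 25 in each group.
- **Discussion (4):** "insufficient research design and small size of sample are the limitations of this experiment".

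The article does not say whether bowel function or SF-36 is measured before treatment, or whether the t-test is run on final values or on changes. The one grading that precedes treatment, into severe, moderate and mild, appears in section 2.1 under the study group's nursing only.

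**The concern.** Recovery has meaning only relative to where a patient started, and the document itself describes patients who differ in severity. The one method it names for continuous data takes no account of that.

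Two things follow if a starting value predicts the outcome. Variation between patients that could have been explained stays in the residual, so the trial detects less than 50 patients could show. Any chance difference between the groups at entry also passes into the estimate in proportion to that correlation. With the sample fixed at 50, the choice of analysis is one of the few ways left to gain precision without enrolling more patients.

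**Working it through.** The plan states no power, effect size, SD or correlation, so there is no figure of its own to reproduce.

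**Inputs from the document:** n = 25 per group; alpha 0.05 (sidedness is not stated; two-sided is assumed here).

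**Assumed inputs:** a standardised effect d = 0.6 SD, and a correlation r between the baseline and final value of the same measure of 0.2, 0.3, 0.5 or 0.6.

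**Unadjusted t-test.** Noncentrality = d × √(n/2) = 0.6 × √12.5 = 2.12 on 48 df. Power is 55%. The effect detectable with 80% power is 0.81 SD.

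**ANCOVA on baseline.** The residual SD is multiplied by √(1 − r²), so the noncentrality becomes 2.12/√(1 − r²) on 47 df, and the detectable effect becomes 0.81 × √(1 − r²). The number of patients that an unadjusted analysis would need for the same precision is 50/(1 − r²).

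| r (assumed) | √(1 − r²) | Noncentrality | Power at 0.6 SD | Detectable effect, 80% power | Unadjusted-equivalent N |
|---|---|---|---|---|---|
| no adjustment | 1 | 2.12 | 55% | 0.81 SD | 50 |
| 0.2 | 0.980 | 2.17 | 56% | 0.79 SD | 52 |
| 0.3 | 0.954 | 2.22 | 59% | 0.77 SD | 55 |
| 0.5 | 0.866 | 2.45 | 67% | 0.70 SD | 67 |
| 0.6 | 0.800 | 2.65 | 74% | 0.65 SD | 78 |

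At r = 0 the only cost of adjusting is the lost degree of freedom: power is 54.7% either way, to one decimal.

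**Chance imbalance.** The standard error of the difference in baseline means is √(2/25) = 0.28 SD. An imbalance of one standard error moves the unadjusted estimate by r × 0.28 SD, which is 0.14 SD at r = 0.5. ANCOVA removes this component.

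**If the t-test is meant for change scores.** The SD is multiplied by √(2(1 − r)), which is 1.183 at r = 0.3, 1.000 at r = 0.5 and 0.894 at r = 0.6. The noncentralities are 2.12 divided by these, on 48 df. Power at 0.6 SD is then 42%, 55% and 64%, against 59%, 67% and 74% for ANCOVA. At r = 0.3 the change score does worse than the final value alone (42% against 55%).

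**Which outcomes this touches.**

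- Defecation time is a natural continuous variable, and the eight SF-36 domains are scores.
- Distension, constipation and incontinence have no stated scale. If they are scored, the point applies; if they are yes/no or graded categories, they go to the chi-square test and it does not.
- Satisfaction with the nursing received has no pre-treatment value to adjust for.

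**The case against.** The strongest objection is that nothing in the Statistical analysis section is wrong. A two-group t-test is valid under randomisation, adjustment is often left to an analysis plan, and this is a condensed article. The validity point stands, and it limits the claim to efficiency and chance imbalance. The deferral point is weaker, because the article does not leave the method open. It names one test for continuous variables, and the layout of Table 1 fits that test. Suggesting a better method than the one named is different from noting an absent detail. A fuller plan that is not shown could still specify adjustment.

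Other objections stand and narrow the point:

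- A reader might infer that baseline values are collected and then thrown away. The document does not support that. It does not say that they are collected, and a t-test on change scores would use them, though inefficiently.
- A reader might infer that the whole recovery endpoint suffers. Part of it may be categorical, and much of the gain may fall on the secondary SF-36 domains.
- Quoting only correlations of 0.5 and above would overstate the gain. At 0.2 it is about 2 percentage points of power.
- It is tempting to add that defecation time is skewed and should be analysed on the log scale. The document gives no distribution or SD for it. The advantage of logs depends entirely on the spread one assumes, so no figure is claimed here.
- Severity cannot simply be added to the model, because its grading is described for the study group only.

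**Conclusion.** The point holds as a cheap improvement to a stated method; the analysis section contains no error on this score. The t-test makes no use of a starting value unless it is run on change scores, which the article does not say, and change scores have less power than ANCOVA at every correlation considered.

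For a 0.6 SD effect, the gain in power from baseline adjustment runs from about 2 percentage points (r = 0.2) to about 19 (r = 0.6). The size rests on the assumed effect and correlations, on two-sided alpha 0.05, on complete data in 25 patients per group, and on a baseline measured before allocation. Because the possible loss from adjusting is negligible even at r = 0, the recommendation does not depend on which correlation turns out to be true.

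**What to change.** 1. State that the bowel items and SF-36 are recorded in all 50 patients before allocation.
2. Replace the t-test sentence for continuous variables with: *Continuous outcomes are compared by ANCOVA with treatment and the baseline value of the same measure, reported as adjusted differences with 95% CIs.* Outcomes with no baseline value, such as satisfaction, keep an unadjusted comparison.
3. Add baseline and adjusted-difference columns to Table 1.
4. Include severity as a covariate only if it is graded before allocation in both groups, and say so.

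The cost is a change of wording, one degree of freedom and, if baseline is not already taken, one assessment with a questionnaire per patient at entry. Baseline values cannot be recovered once the nursing has begun, so this needs to be settled before enrolment.

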## Result

3

Comparison of clinical parameters between the 2 groups will be shown in Table 1.

**Table 1 T1:** Comparison of clinical parameters between the 2 groups.

Study group (n = 25)	Control group (n = 25)	*P* value
Bowel function		
Abdominal distension		
Constipation		
Defecation time		
Fecal incontinence		
Quality of life		
Physical functioning		
Role-physical		
Bodily pain		
General health		
Vitality		
Social functioning		
Role-motional		
Mental health		

## Discussion

4

The bowel dysfunction is one of the most familiar problems in the patients with SCI.^[13,14]^ In the early injury stage, the anal sphincter and rectum internal layer are in the stage of total incontinence. After the acute phase, the voiding reflex recovers with the recovery of the lumbosacral central spinal cord.^[15]^ The right side of colon and the bowel are peristalsis supplied by the vagal innervation, so that the feces can be transported to large intestine. After the SCI, patients may have several problems, for instance, reduced sensation and muscle strength, and impaired respiratory as well as other functions.^[16]^ Specifically, SCI can lead to the high spasticity and paralysis of anal sphincter, or lead to the voiding dysfunction. The participation of pelvic and abdominal muscles and effective movement of bowel are essential for the normal defecation. According to the severity of intestinal dysfunction and SCI, we develop a set of nursing intervention based on the quantitative evaluation for the intestinal dysfunction patients after SCI, so as to make nursing more efficient and targeted. Nevertheless, insufficient research design and small size of sample are the limitations of this experiment. The effectiveness of nursing intervention based on quantitative evaluation needs further study.

## Conclusion

5

Nursing intervention based on the quantitative evaluation can improve the quality of life and recovery of intestinal function for the neurogenic intestinal dysfunction patients after SCI.
